### Rationale for selecting primary care versus ED setting

Providing a BI in the ED setting has a number of advantages. For example, the ED is where individuals with substance-related injuries and acute medical problems present for urgent care. This setting maximizes the chance for a “teachable moment” and has more “high risk” individuals with a greater potential for high cost medical care use. Although the prevalence of illicit drug use is greater in the ED [31], primary care sees a larger number of individuals on an annual basis and has a service system more amenable to ancillary behavioral treatments because of its chronic illness focus. Furthermore, risk reduction in this setting can potentially prevent higher cost ED and hospital visits since patients in safety net medical settings are less likely to utilize primary care in a ‘health maintenance’ fashion and more likely to schedule primary care appointments on an ad hoc basis when they have emergent medical problems. In individuals with hazardous drug use, some of these problems are substance-related, creating ‘teachable moments’ like those seen in patients seeking care in the ED. Finally, a host of prior studies have shown that integration of mental health into primary care is clinically and cost effective [32]. Integration of interventions for substance abuse into primary care could have similar advantages, especially since substance-related medical problems could be addressed at the same time [33-35].

### Assessing public-health benefits of the intervention

As described earlier, providing SBIRT services to a sizable proportion of individuals with hazardous substance abuse in the ambulatory primary care setting has the potential to result in a sizable public health benefit [15]. That is, the public health benefit, or population attributable benefit, is far greater if one affects many people in a small way than fewer people in a larger way. As such, it is important to examine this benefit, especially at a time when providers, health care administrators, and policy makers are being increasingly required to rein in health care costs that are spiraling upward while resources for public health care are diminishing [36]. Quantifying the impact of brief interventions on the cost of health care, public safety, and mortality represent critical information needed to inform policy and program planning at the local, state, and national levels. The current study was designed to respond to this need by making preliminary estimates of the public health-related benefits of the intervention including changes in use of inpatient, emergency department, and outpatient medical services; arrests; HIV infection; mortality; and costs through the use of administrative data.

### Keeping the assessment brief but accurate

To enhance external validity, we are limiting the intensity and frequency of assessment to bridge the distance between a traditionally rich and extensive efficacy study assessment battery and what might more routinely be performed as part of quality assurance when an SBIRT program is implemented. This decision also enhances internal validity because prolonged assessor contact with significant focus on substance-related measures (in the usual care arm) may have an unintended therapeutic effect as noted by other experts [15,37-41]. That is, the more elaborate assessment of the typical efficacy study would likely last longer than the actual BI itself and might confound the comparison condition of ECAU. As such, we are limiting assessment to 30 minutes, a duration which has been shown to not have an intervention effect in recent analysis [42]. At the same time, we are supplementing our assessment with administrative data that will allow us to verify medical services received and whether individuals had participated in substance abuse treatment recently or had received a BI outside of this study. Our access to medical records will also help us determine whether individuals with urine screens positive for opiates might be receiving prescription opiates for related painful medical conditions as well as whether there is documentation of excess use, withdrawal symptoms, requests for early prescriptions, or visits to the ED to obtain more opiates that can be used to recode self-reported opiate use gathered during assessment.

### Selecting study sites

The present study is sited in primary care clinics affiliated with a large urban safety net medical center. One advantage of this siting is that patients receive all of their urgent and emergent medical care at the medical center, making it possible to track medical utilization over time. Practical considerations require that participating clinics serve a high volume of patients and, additionally, have evidence that a reasonable proportion of patients (say, 25% or more) are likely to have problem drug use. Insuring sufficient numbers of women in the sample to maximize generalizability is another important consideration. Initially it was estimated that all study participants could be recruited from the pool of patients who sought treatment at one of four primary care clinics. After the first year, however, we were unable to recruit the numbers of patients suggested by our original estimates, which required us to expand to three additional medical clinics. Furthermore, the economic downturn prompted some clinic infrastructure and service delivery changes at the safety net medical center which operates these clinics, creating additional unanticipated challenges, for example, waiting lists for new patients and deciding to move all female primary care patients without specific obstetric and gynecologic needs to other primary care clinics.

### Specific nature of the intervention

The study employed a total of 17 interventionists. We decided to have social workers who were already employed in each of the clinics conduct the BI as they were more available and less costly than primary care physicians. We began with eight social workers and, as the study evolved, required additional interventionists. We recruited three additional social workers who were working in the clinics, two social workers not working in the clinics, two clinical psychology doctoral students, and two bachelor-level individuals with experience conducting structured clinical interviews.

The intervention consists of a single-encounter BI followed by an attempted single phone booster contact one week later. The BI is delivered using an MI approach following a rich history of successful MI-based SBIRT interventions in primary care and trauma center trials for hazardous alcohol use over the last 15 years [18,43-45]. Also, a central consideration in choosing MI for delivery of the intervention was its documented larger effect sizes with ethnic minorities [46]. With every patient, interventionists perform standard elements or “clinical tasks”. The clinical tasks of the counseling session include orienting patients to the purpose of the session, telling patients their screening results, discussing options for change, and giving patients information about links between drug abuse and medical conditions. Interventionists perform these tasks using the highest quality MI skills of which they are capable. Two examples may serve to clarify how one might perform the clinical tasks using an MI style. One example is, when giving screening feedback, the interventionist uses a standard explanation of the DAST-10 score to help the patient understand the meaning of their score while, at the same time, using specific MI skills to handle any arguing or objections from the patient that may arise upon hearing their score. These skills might include reflecting the patient’s surprise or gleaning from the patient’s arguments apparent personal strengths such as having a genuine concern about whether drugs are hurting him/her. A second example of integrating MI illustrates our effort to enhance the potential “teachable moment” of the protocol. This task involves focusing the interview on specific adverse health consequences of particular drugs. To this end, MI skills such as “Ask-Tell-Ask” might be deployed (e.g., *Ask* patient what he/she already knows about the effects of crack smoking on the lungs. *Tell* patient how crack might be exacerbating their chronic cough, and *Ask* patient what they think about that information). In this patient-centered spirit, the intervention focuses on the drug of most concern to patients who use multiple drugs.

All brief interventions are audio-recorded and are scored by trained coders using the Motivational Interviewing Treatment Integrity (MITI) instrument [47] to monitor potential drift in the MI protocol as well as to assess for Aim 2 levels of fidelity to MI. While all interventionists are required after training to reach and maintain a specified threshold of MI skill, it is expected there will still be adequate variation in MI skills to allow for an analysis of study Aim 2—testing the degree to which fidelity to the BI model is associated with better outcomes.

It is possible that the intervention may be too brief to have a treatment effect for some patients with severe drug disorders. However, the intervention could still contribute to a referral effect in that patients who participated in a BI may be more likely to seek treatment after being referred. Whether to refer a patient to treatment is determined using the DAST-10 score as a guide in concert with the spirit of the patient-interventionist interaction. After the intervention, a referral to treatment is usually offered if the patient is not overtly hostile to the idea and when the DAST-10 score is 6 or greater in accordance with existing norms [21]. A DAST-10 score less than 3 does not generally trigger a referral. For DAST-10 scores between 3 and 5, the interventionist uses their judgment as to whether to refer based on information obtained from the BI. When in doubt, or whenever the patient asks for help, the interventionists refer. In addition, to preserve internal validity, all individuals assigned to the BI group are given the same referral sheet as individuals assigned to the ECAU group.

A booster session has been shown to enhance the effects of a BI [48] and, for this reason, is included in the present study. The booster session consists of a ten-minute follow-up call approximately one week after the initial intervention. During the call, the interventionist references the plan or option decided upon in the initial intervention and uses MI to follow-up on ambivalence about enacting the plan, generating change talk, or committing to specific goals.

### Training the interventionists

Interventionist training was designed to support the provision of consistently high quality BIs across clinics, between interventionists, and within interventionists over time. It consists of an 8 to 16 hour BI workshop supplemented by one hour of individual supervision once a week for the following three to five weeks. During the individualized supervision, trainees receive tailored coaching with the MI trainer (CD) and feedback on their audio-taped role-plays with standardized patients using their MITI scores. The training protocol was designed to be an enhanced version of manualized trainings recognized for their effectiveness that have been conducted both nationally and internationally [18,44,45,49-53].

### Screening and assessment

It is important to be able to identify individuals with problem drug use reliably and validly, and to be able to do so without interfering with day-to-day medical clinic operations. A brief screening procedure was devised to assess individuals for eligibility in the study; it involves the patient completing a form which includes eligibility criteria and two screening questions: (i) to identify any illicit drug use in the past three months, and (ii) to identify any non-prescribed medication use in the past three months. The screening questions are based on a single-item screening test found to reliably identify drug use in a primary care population [24]. Screen-eligible individuals interested in enrolling in the study are then consented and assessed in a private area on-site with a modified battery (see below) and those randomized to the BI group are provided a BI at the earliest possible time, usually the same day.

### Assessment battery and table

The DAST-10 was selected as an instrument to assess substance abuse severity because of its widespread use over the last decade (including the SAMHSA SBIRT trial in Washington State), its known psychometric properties, the fact that it is self-administered and takes less than 5 minutes to complete, and because it provides a range of scores that have known convergent validity with substance abuse severity defined by other clinical means [21]. This latter characteristic is crucial in stratifying the sample for drug abuse severity prior to randomization.

In order to be consistent with the majority of extant BI studies on alcohol and drug abuse, we use a 12-month assessment window and conduct assessments at baseline, 3, 6, 9, and 12 months. Research assistants conduct follow-up interviews and are blinded to a participant’s intervention versus control group status. Assessments are carried out in-person whenever possible, with phone interview as a backup option. Vigorous outreach is used to complete assessments. The assessments are brief to minimize any unintended intervention effects and to allow the BI to be conducted as close as possible to the screening procedure although we recognize that in-person assessments could potentially contribute to an unintended effect favoring the comparison group. Assessment measures and the times they are administered are summarized in Table 1.

**Table 1 T1:** Assessment measures

**Measure**	**Baseline**	**3 months**	**6 months**	**9 months**	**12 months**
Preliminary Informed consent + 1-item screen	X				
Full informed consent	X				
HIPAA Authorization	X				
Consent for Follow-up Procedures	X				
Release of Information	X				
DAST-10	X				
Thoughts about Drug Use	X	X	X	X	X
Addiction Severity Index (ASI) -Lite	X	X	X	X	X
Treatment Services Review (TSR)	X	X	X	X	X
HIV Risk-Taking Behavior Scale	X	X	X	X	X
EQ-5D-3L	X	X	X	X	X
Urine Sample	X	X	X	X	X

We supplement self-report data collected from participants with data from several administrative sources. These are summarized in Table 2. For the administrative sources, the follow-up time ranges from a minimum of 12 months to a maximum of 24 months, depending on data availability during the time of the study. Obtaining data for a minimum of 12 months will facilitate estimates of public health effects, given prior results of functional effects for substance abuse interventions [13,53,54].

**Table 2 T2:** Administrative data sources

**Data source**	**Owners of data**	**Description of data records**	**Derived measures**
Treatment and Assessment Report Generation Tool (TARGET)	Washington State Department of Social and Health Services (DSHS), Division of Behavioral Health and Recovery (DBHR)	Record of participation in publicly-funded chemical dependency treatment or detoxification services	- Number of days with outpatient treatment visit
			- Number of days of inpatient stays
			- Number of detoxification admissions
Medical records	Medical Center Site of Study	Health care encounters by date, diagnoses	- Number of inpatient hospital stays/days
			- Number of emergency department visits
			- Number of outpatient visits
			- HIV diagnosis date
			- Hepatitis diagnosis date
Billing records	Medical Center Site of Study	Cost of health care encounters by date	Cost of
			-Inpatient hospital stays
			- Emergency department visits
			- Outpatient visits-
Comprehensive Hospital Abstract Reporting System (CHARS)	Washington State Department of Health (DOH)	Hospital discharge data, length of stay, up to 17 diagnoses, demographic information	- Number of inpatient hospital stays/days
Washington State Patrol Arrest Records	Washington State Patrol	All arrests in Washington State including arrest date, nature of offense, level of offense	- Number and type of felony arrests
			- Number and type of gross misdemeanor arrests
Washington State Death Records	Washington State DOH Vital Records	Information about decedent (e.g., age, date of birth, race), place of death, cause-of-death codes, injury information	- Date of death
			- Cause of death

### Choosing the primary outcome variables

Outcome variables were selected specific to each of the study’s aims:

#### Aim 1

For the first aim—to examine whether BI is effective at improving drug use, psychiatric outcomes, select psychosocial outcomes, and attendance in drug abuse treatment—it is important to reliably capture changes in drug use as well as in other variables in as brief a period of time as possible. Because of its widespread use, brevity, and reliability, the validated short form of the Addiction Severity Index (ASI), the ASI-Lite [55], was selected for this purpose along with the Treatment Services Review (TSR) [56]. To further minimize time burden on participants, we only administer items required to compute the ASI composite scores (half the total items) [55].

In order to identify changes in illicit drug use, we use items from the ASI drug section to measure days of any drug use. A urine toxicology screen is used to supplement participants’ responses. In addition, we use the ASI composite scores as comprehensive measures of participants’ medical, psychiatric, legal, family/social, and employment status. The HIV Risk-Taking Behavior Scale is used to assess risk-taking behavior among intravenous drug users [57] and the EQ-5D-3L is used to measure health status [58]. Administrative data are used to supplement ASI data on legal (e.g., arrests) effects. Changes in attendance in drug treatment are obtained from the TSR as well as from state administrative chemical dependency treatment records.

#### Aim 2

The second aim—to test whether fidelity to the BI model is associated with better outcomes—requires a reliable way to assess fidelity. Because of is reliability, cost effectiveness, and brevity, the MITI, which provides a standardized way to rate session audiotapes for degree of MI content, was selected for this purpose [47]. Outcomes for this aim include changes in illicit drug use and drug treatment attendance as measured in the first aim.

#### Aim 3

For the third aim—to estimate the impact of BI on select public health outcomes that are directly related to the hazardous effects of illicit drug use—it is important to identify objective measures reflective of the consequences of illicit drug use. Because of their established tie to illicit drug use, we selected changes in utilization of health care services (including ED visits, inpatient hospitalizations, and hospital days), arrests, and death, as captured in state administrative records [59,60].

#### Aim 4

The fourth aim—to estimate the cost of the intervention, potential cost offsets, and its incremental cost effectiveness —requires valid cost data. The cost of the intervention includes the cost of personnel, materials, and locations for start-up and implementation activities required to screen for drug use and provide a BI. Potential cost offsets will be examined for emergency room visits, outpatient visits, and hospital admissions. The cost measure for all of these medical services includes the direct and indirect costs of providing medical care from the provider perspective. If indicated by study results, we will also assess cost offsets generated by reductions in arrests. If the BI is found to reduce drug use, we will further estimate the incremental cost of the BI intervention compared to its incremental effect on drug use.

### Data analysis

Analyses will compare outcomes for the BI and ECAU groups following the intent-to-treat principle. If indicated, these models will take into account baseline differences between the two groups. Time trend models will be used to examine temporal effects, specifying time of assessment as a categorical variable (baseline, 3, 6, 9, and 12 months). Because assessments are nested within patients and patients are nested within clinics and interventionists, analyses will be conducted with linear mixed models. Clinics will be treated as fixed effects, as they were purposively sampled. In contrast, interventionists were assigned to patients based on availability when a BI had to be administered. For interventionists, random effects will therefore be specified and tested.

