### Study design

This study is a two-group randomized prospective trial with blinded assessments (See Figure 1), approved by the University of Washington Institutional Review Board (Protocol #34892). Written informed consent is obtained from patients for study participation including permission to use unidentified information collected from them in study reports. Approximately 1,000 individuals presenting for scheduled medical care at one of seven designated primary care clinics who endorse problematic drug use when screened during that visit and then randomized in a 1:1 ratio to BI versus ECAU using a stratified permuted block randomization procedure. The purpose of the stratification is to balance random assignment by three factors known to be related to substance abuse outcomes including severity of drug problem [21], presence of a co-occurring mental disorder [22], and readiness to change [23].

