### Defining the population

As stated earlier, the population of interest is individuals seeking primary care treatment in a safety net medical center setting. Screening procedures are designed to identify individuals with problem drug use along a continuum of severity. Study inclusion criteria include adults age 18 and over; having used an illegal drug or used a prescription medication for nonmedical reasons at least once in the past three months [24] (equivalent to a DAST-10 score greater than 0 [25,26]); currently receiving care in the primary care clinic and planning to continue such care for the next year; English speaking and able to read and understand screening and assessment forms (6^th^ grade literacy); and having a phone, easy access to a phone with voicemail, or access to e-mail in order to facilitate scheduling.

To enhance external validity there are few baseline exclusion criteria. They include having attended formal treatment for substance abuse (excluding self-help groups such as Alcoholics Anonymous) in the past month; life-threatening medical illness (potential mortality in next year); severe cognitive impairment or active psychosis interfering with cognitive ability to process the BI (based on performance during consent and assessment); or active high risk suicidality [27].

There are two reasons for not excluding patients with the most severe drug problems from this trial. First, although some studies of BI for alcohol have found that patients with alcohol dependence responded less well to a BI than patients with less severe abuse or hazardous drinking, Field recently found that patients with alcohol dependence responded better to a BI than those with less severe problems [28] and Cobain found hospital-based BI effects to be independent of baseline dependence or medical comorbidity [29]. Second, even if a BI were inadequate as a stand-alone treatment for safety net patients with severe drug dependence, BI may prove to be a valuable referral mechanism for getting these patients to more intensive chemical dependency treatment, as it did in WASBIRT [30]. For these reasons, we include individuals across the full range of drug use and abuse in the present study. To balance drug use severity across BI and control groups, we use the DAST-10 score as a stratifying variable.

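### Covariate adjustment is left to observed baseline differences, a trigger that would almost never pick the three stratification factors; the covariates should be fixed in advance

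*Protocol article*

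**What the plan says.** The Study design section describes patients as "randomized in a 1:1 ratio to BI versus ECAU using a stratified permuted block randomization procedure". It gives the reason: "The purpose of the stratification is to balance random assignment by three factors known to be related to substance abuse outcomes". The factors are severity of the drug problem, a co-occurring mental disorder and readiness to change. Under Defining the population the severity factor is identified: "we use the DAST-10 score as a stratifying variable".

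The Data analysis section has one sentence on covariates: "If indicated, these models will take into account baseline differences between the two groups". No threshold, test or list of candidate covariates goes with it. The terms that the section does name are:

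- time, "specifying time of assessment as a categorical variable (baseline, 3, 6, 9, and 12 months";
- clinic: "Clinics will be treated as fixed effects, as they were purposively sampled";
- interventionist: "For interventionists, random effects will therefore be specified and tested".

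The Power analysis section refers to covariates other than the intervention indicator but does not name them.

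**The concern.** The conditional sentence is a stated rule, so it can be judged as one. It has two weaknesses in this design.

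First, whether and for what the model adjusts depends on how the arms turn out to differ at baseline. After randomisation such differences are chance, and their size says nothing about whether a covariate predicts outcome. With no criterion, the decision that adjustment is indicated is left to the analyst once data are in hand.

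Second, the rule works against the stratification. Permuted blocks within strata remove imbalance in exactly the three factors chosen for their relation to outcome, so an imbalance trigger passes over them and admits other variables by chance. If those strata are prognostic and are left out of a between-arm comparison at follow-up, the model-based standard error takes no credit for the balance that the design secured.

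A related gap concerns the baseline value of the outcome. Baseline is one level of categorical time, but the article does not say whether the two arms share a mean there. That choice determines how efficiently the baseline measurement is used.

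**Working it through.** The plan gives no figure for the effect of adjustment. The R² values in the Power analysis section describe correlation between the intervention indicator and the covariates. They do not describe how well covariates predict outcome, so they cannot be used here.

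**Inputs from the article.** 1,000 enrolled, 1:1, stratified permuted blocks on three factors, 75% response, 375 per group analysed at 12 months, two-sided alpha 0.05.

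**Assumed.** Three binary strata, blocks of 4, a continuous outcome with variance 1, responders missing at random, and strata explaining R² = 0.10, 0.20 or 0.30 of outcome variance. Six further baseline covariates are examined. The trigger is a baseline test with p < 0.05. The effect is set to give 80% power unadjusted: (1.960 + 0.842) × √(2/375) = 0.205 SD.

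**Step 1: what the trigger selects.** In simulation the stratifiers were flagged in 0% of trials. At least one of the six other covariates was flagged in about 26%, as expected from chance alone: 1 − 0.95⁶ = 0.265.

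**Step 2: error rate and power** (4,000 null and 2,000 alternative replicates per row, no other prognostic covariate):

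| R² of strata | Type I error, trigger | Type I error, strata always in | Power, trigger | Power, strata always in | Loss (points) |
|---|---|---|---|---|---|
| 0.10 | 0.043 | 0.053 | 0.803 | 0.833 | 3 |
| 0.20 | 0.032 | 0.047 | 0.822 | 0.884 | 6 |
| 0.30 | 0.027 | 0.053 | 0.842 | 0.923 | 8 |

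**Step 3: check by formula.** Blocking removes the strata's contribution among all randomised. Random 25% non-response restores a quarter of it. The true variance of the unadjusted difference, relative to what the model assumes, is therefore 1 − R² + 0.25R² = 1 − 0.75R², or 0.925, 0.850 and 0.775. Type I error is 2[1 − Φ(1.960/√(1 − 0.75R²))] = 0.042, 0.034 and 0.026, in line with the simulation. With the strata in the model, the equivalent number per group is 375/(1 − R²) = 417, 469 and 536.

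**Step 4: baseline outcome.** Take one baseline and one follow-up measurement with equal variance and correlation ρ. A change contrast with free baseline means has variance proportional to 2(1 − ρ); conditioning on baseline gives 1 − ρ². The ratio of conditioning to change is (1 − ρ²)/[2(1 − ρ)] = (1 + ρ)/2. No ρ is given in the article; for assumed values:

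- ρ = 0.3: 0.91/1.40 = 0.65
- ρ = 0.5: 0.75/1.00 = 0.75
- ρ = 0.7: 0.51/0.60 = 0.85

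**Step 5: the two losses do not add.** A time-constant stratifier cancels from a within-patient change. In a random-intercept model with 1,000 patients, blocked strata and free baseline means, the standard error of the 12-month arm-by-time contrast was 0.0631 without stratifiers and 0.0631 with them. With 25% of follow-up visits missing at random it was 0.0685 and 0.0684. The losses in step 2 therefore apply to a between-arm comparison at follow-up, and the loss in step 4 applies to a change contrast.

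**The case against.** The strongest reply is that the article is a condensed account. It gives no covariate list, its power section presumes covariates that it does not name, and a full protocol or analysis plan may well include the stratifiers. A reader might infer that the three factors are excluded from the model. The article does not say so, and that reading is not supported. What can be said is that the Data analysis section does not commit to them and that its one adjustment rule would not select them.

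A reader might also infer that the treatment effect is a change score with separate arm means at baseline. That is not stated either: baseline is a level of time in models meant to describe temporal effects, and a common baseline mean fits the same wording. For the same reason it would be wrong to say that the baseline outcome is used only when adjustment is indicated, since the baseline assessment is in the time-trend model in any case.

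Finally, a reader might expect data-driven covariate choice to inflate type I error. Applied mechanically, it did not: the test was conservative. Discretion over when to adjust is a separate risk that the simulation does not measure.

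These replies limit the point but do not rescue the sentence. A fuller plan that followed it would still be adjusting on observed imbalance.

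**Conclusion.** The point holds in a limited form. The stated rule is conditional and has no criterion, and it is poorly matched to a design that blocks on prognostic factors. For a between-arm follow-up comparison that omits the strata, the cost is about 3 to 8 points of power and a type I error of 0.043 to 0.027 instead of 0.05. This rests on strata explaining 10% to 30% of outcome variance and on a linear model with a continuous outcome, none of which the article supplies. If instead the contrast is change from baseline with free arm means, the stratifiers add almost nothing. The avoidable loss then lies in how baseline is handled: conditioning has 0.65 to 0.85 of the variance, for an assumed ρ of 0.3 to 0.7. The two costs are alternatives and should not be summed. Neither biases the comparison towards the intervention, so this is a worthwhile improvement and not a threat to validity.

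**What to change.** Replace the conditional sentence in the Data analysis section with:

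> All models include the three randomisation stratification factors as prespecified covariates, regardless of observed balance. The baseline value of the outcome is handled either as a covariate, with follow-up times 3, 6, 9 and 12 months as outcomes, or by constraining the two arms to a common baseline mean. Covariates are not selected by observed baseline differences.

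One of the two baseline options should be chosen and named before data are compared by arm. The change needs no new data: the stratification factors must be known before randomisation, and Table 1 shows the DAST-10 and the ASI-Lite collected at baseline. The cost is a few words of text and a few model degrees of freedom.
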